### Safety assessment

All adverse event occurrences will be informed immediately to the clinical research coordinator and the principle investigator. Together with the acupuncturist in charge, they will evaluate, consult on the case, and take proper action. All expected (feeling faint after acupuncture treatment, stuck needles, broken needles, minor burning and vesicles during or after warm acupuncture, hematoma and bruising after needle removal) and unexpected (exacerbation of lymphedema, inflammation, infection, local or systematic reaction) adverse events will be reported immediately and recorded in the case report form (CRF). Any significant change of health state after baseline will also be recorded as an adverse event. All adverse events will be closely monitored and followed up until stabilization or resolution. Complete blood count, liver function, kidney function, and electrocardiography will be assessed at baseline and at week 8 to detect adverse events.

### Sample size calculation

According to the results of our preliminary trial (9 participants in the LDA group, 7 participants in the LA group, and 10 participants in the WL group), the biggest circumference difference after 20 treatments was 2.34 ± 1.6 cm, 3.32 ± 1.53 cm, and 3.74 ± 1.1 cm in the LDA, LA, and WL groups, respectively. According to the formula:$$ \mathrm{n}={\Psi}^2\left(\sum \left({Si}^2\right)/K\right)/\left[\sum {\left(\overline{Xi}-\overline{X}\right)}^2/\left(\mathrm{K}-1\right)\right] $$α = 0.05β = 0.10K = 3Ψ: K = 3, degree of freedom V1 = K–1 = 2; degree of freedom V2 = N–1, N is unknown, assume N as ∞, according to the T distribution critical values table when α = 0.05 and β = 0.10: Ψ α, β, K–1, ∞ = 2.52$$ \overline{Xi} $$ and Si represent mean number (X1 = 2.34, X2 = 3.32, X3 = 3.74) and standard deviation (S1 = 1.6, S2 = 1.53, S3 = 1.1) of group i according to the preliminary trial.$$ \overline{\mathrm{X}} $$= (X1 + X2 + X3)/K = (2.34 + 3.32 + 3.74)/3 = 3.13

The result of calculation was 30 participants in each group. Assuming a 20% dropout rate, a total of 108 participants are required with 36 participants in each group.

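### The printed sample-size formula gives 26 per group, not 30, and the 20% dropout allowance multiplies by 1.2 instead of dividing by 0.8; the errors offset, so 108 still meets the 90% target for the overall test

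*Protocol article*

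**What the plan says.** All of this is in one section of the protocol article, Sample size calculation. It uses a preliminary trial with "9 participants in the LDA group, 7 participants in the LA group, and 10 participants in the WL group", and takes from it the largest inter-limb circumference difference after 20 treatments. The group values enter as "mean number (X1 = 2.34, X2 = 3.32, X3 = 3.74" and "standard deviation (S1 = 1.6, S2 = 1.53, S3 = 1.1" (in cm, in the order LDA, LA, WL). Alpha is 0.05, beta 0.10 and K = 3. The multiplier is looked up with "degree of freedom V1 = K–1 = 2" and the second degrees of freedom taken as infinite ("N is unknown, assume N as" infinity), giving "Ψ α, β, K–1, ∞ = 2.52".

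The formula is n = Ψ²(ΣSi²/K) / [Σ(Xi − X̄)²/(K − 1)]. The stated outcome is "The result of calculation was 30 participants in each group", followed by "Assuming a 20% dropout rate, a total of 108 participants are required with 36 participants in each group".

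**The concern.** The section presents 30 as what the formula returns, not as a rounded or padded figure. Since every input is printed, the result can be checked, and it does not reproduce. The step from 30 to 36 is a second, separate problem: adding 20% to a number does not protect it against a 20% loss.

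This section is the justification for randomising 108 people. If its figures do not follow from its method, the 90% power it targets is not shown to be met until someone redoes the calculation. Two errors in sequence could have left the trial too small or made it needlessly large, so the net effect has to be worked out.

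**Working it through.** **Inputs** (all from the Sample size calculation section): means 2.34, 3.32, 3.74; SDs 1.6, 1.53, 1.1; Ψ = 2.52; K = 3; dropout 20%.

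**Step 1: the formula as printed.**
- Grand mean: (2.34 + 3.32 + 3.74)/3 = 3.1333 (the section prints 3.13, which is correct to two decimals).
- Within-group term: ΣSi²/K = (2.5600 + 2.3409 + 1.2100)/3 = 6.1109/3 = 2.0370.
- Between-group term: Σ(Xi − X̄)²/(K − 1) = (0.6294 + 0.0348 + 0.3680)/2 = 1.0323/2 = 0.5161.
- n = 2.52² × 2.0370/0.5161 = 6.3504 × 3.9466 = 25.06, so **26 per group**. The stated figure is 30.

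**Step 2: is a printed input at fault?** Ψ = 2.52 is sound. A non-central chi-square with 2 degrees of freedom, alpha 0.05 and 90% power needs λ = 12.65, and √(12.65/2) = 2.515. To reach 30, Ψ would have to be √(30 × 0.5161/2.0370) = 2.757.

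**Step 3: other ways of reading the same inputs.**

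| Variant | n per group |
|---|---|
| Grand mean rounded to 3.13 | 25.06 |
| Grand mean weighted by pilot group sizes | 25.06 |
| Variance pooled by degrees of freedom | 24.3 |
| Square of the average SD | 24.5 |
| Ψ for finite error degrees of freedom (75 to 87) | 26.0 to 25.9 |
| Largest SD (1.6) used for all groups | 31.5 |
| Between-group divisor K instead of K − 1 | 37.6 |

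None gives 30. Values near 30 appear only with inputs that the section does not state: error degrees of freedom of 20 give 29.2, and alpha of 0.025 gives 29.1.

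**Step 4: cross-check by exact power.** One-way analysis of variance, non-central F with 2 and 3(n − 1) degrees of freedom, and non-centrality n × 1.0323/2.0370:

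| n per group | Power, overall test |
|---|---|
| 25 | 88.7% |
| 26 | 90.0% |
| 28.8 | 92.9% |
| 30 | 93.9% |

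This agrees with the formula: 26 is the smallest size that reaches 90%.

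**Step 5: the dropout step.**
- The plan's figure reproduces as 30 × 1.2 = 36, and 36 × 3 = 108.
- Remaining after 20% loss: 36 × 0.8 = 28.8 per group.
- To keep 30: 30/0.8 = 37.5, so 38 per group, 114 in total.
- To keep 26: 26/0.8 = 32.5, so 33 per group, 99 in total.

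**Step 6: net effect.** The planned 36 per group exceeds 33, and 28.8 exceeds 26.

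**Step 7: what the power figure does not cover.** On the same pilot values, for LDA versus LA, the difference is 3.32 − 2.34 = 0.98 and the pooled SD is √((1.6² + 1.53²)/2) = 1.565. With 28.8 per group, an unadjusted two-sided 5% t-test has about 65% power.

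**The case against.** The best defence is that nothing in the conduct of the trial depends on this. The 90% target for the overall test survives the full 20% loss, and the shortfall against 30 is only 1.2 participants per group. That is right, and it makes this a correction to the reported calculation. Rounding up to 30 for safety would be legitimate, but the text calls 30 the result of the calculation and mentions no margin. One unconfirmed possibility is that dropout was applied twice: 25 × 1.2 = 30, then 30 × 1.2 = 36.

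A reader might infer three stronger points that the document does not support:
- **The plan breaks a promise to retain 30 evaluable participants per group.** The section never states a retained number. It states a requirement of 30 and an enrolment of 36. That 30 should remain is a fair inference, not a quoted claim.
- **The power of 108 participants cannot be known.** Every input is printed, and the power follows from them, as shown above.
- **The overall test is underpowered.** It is not, on the pilot values.

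It can also be said that 28.8 is not the number analysed. The Statistical analysis section carries the last observation forward and keeps the end-point count at the starting number, so the full analysis set could hold close to 36 per group. This stands as a limit on wording: 28.8 is the number with complete data. Carried-forward values do not, however, restore the information lost, so 28.8 remains the sensible basis for planning.

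**Conclusion.** Both errors are established from the section's own figures. The formula gives 26 where 30 is stated, a gap of 4 per group. The dropout step gives 36 where a requirement of 30 would need 38, a gap of 2 per group or 6 in total. Because the first error overstates the need and the second understates the allowance, 36 per group ends 3 above the 33 that the method actually requires.

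This rests on the pilot means and SDs being the true values, on equal group sizes, and on an unadjusted overall comparison of three groups. The pilot quantity is a post-treatment level, whereas the primary outcome is change from baseline, compared by ANCOVA. The power of about 93% at 28.8 per group therefore says nothing direct about the primary analysis. Nor does it cover the stated aim of comparing the two acupoint combinations.

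**What to change.** Rewrite the closing sentences of the section and leave enrolment unchanged. Suggested content: the formula gives 26 per group; allowing for 20% dropout (26/0.8) gives 33 per group, 99 in total; 36 per group (108) are enrolled, which leaves about 28.8 per group with complete data. Alternatively, if 30 came from a deliberate margin or from another input, state it, and correct the dropout step to division by 0.8.

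If a power of about 93% is quoted, add that it holds only for the unadjusted overall three-group test on the pilot's post-treatment largest circumference difference. Say that it does not apply to the ANCOVA of change from baseline or to LDA versus LA (about 65% on the same values, unadjusted two-sided 5% t-test).

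As an optional tidy-up, the second degrees of freedom should read K(n − 1), not N − 1. It was set to infinity in the lookup, and using the finite value still gives 26.

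The cost is one corrected paragraph.

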### Statistical analysis

A full analysis set will include all randomized participants who received at least one treatment and one follow-up. The principle of the last observation carried forward will be used in the case of missing data. The number of end point evaluations in each group will be kept the same as the number of participants in each group at the beginning of the trial.

A per-protocol set will include the following: (1) participants who meet the criteria of the protocol, (2) participants with measurable primary outcomes, and (3) participants without major violation of the protocol.

The statistical analysis of the primary outcome will be analyzed with a full analysis set and per-protocol set separately. The safety set will include all randomized participants who received at least one treatment.

Data will be coded and entered into SPSS (v.22) for statistical analysis. The Cochran–Mantel–Haenszel test will be used for analysis of center effect. Descriptive statistics of all sociodemographic and clinical data will be included. Continuous variables will be reported using mean and SD for normally distributed data or median and range for skewed data. Categorical variables will be expressed as number and percentage. For outcome measures, the mean differences from baseline values to the end of treatment will be compared using ANCOVA. Repeated measures analysis of variance (R-ANOVA) will be used to assess the inter-limb circumference difference, inter-limb volume difference and skin hardness between the three study groups. Inter-group differences in categorical data (CTCAE 4.03, stages of lymphedema) will be assessed using the χ^2^ test or Fisher’s exact tests (two-tailed), as appropriate. Linear mixed models (for continuous outcome variables) and generalized estimating equations (for categorical outcome variables) will be used to examine the change of intensity in inter-limb circumference difference and SF-36. *P* values of <0.05 will be considered statistically significant.

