### Interventions

The acupuncture groups (LA and LDA group) will receive acupuncture treatments three times per week for a total of 20 treatments. The treatments will be performed by practitioners who hold a Chinese medicine practitioner license from the Ministry of Health of the People’s Republic of China. Practitioners will be instructed to achieve de qi sensation and then the needles will be retained for 30 min. Disposable, sterilized stainless-steel acupuncture needles will be used in the acupuncture groups (Huatuo disposable acupuncture needle, Suzhou Medical Co., Jiangsu, China, 0.25 × 40 mm). During the needle retention period, moxa cones (Mac mini needle moxa, Tianjin HaingLimSouWon Medical Co., Ltd., Tianjin, China, 2 cm) will be placed on the handle of the needles at specific acupoints. A piece of hard paper will be placed on the acupoint to prevent burning of the participants from falling ashes. The moxa cones will then be burned to delivery warm acupuncture. Additional hard paper will be added if the patient feels uncomfortable with the increasing temperature. All treatment that may affect the result of the study will be restricted, including surgical interventions, acupuncture, blood-letting, diuretics, exercise, complete decongestive therapy, compression therapy, and manual lymphatic drainage. Treatments that the participants had been using prior to the trial may be allowed at the discretion of the investigator after evaluation of the patient’s condition.

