### WL group

Patients in the WL group will not receive any acupuncture treatment during the study. However, for ethical consideration, 20 free acupuncture treatments will be offered after the study is completed.

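### The full analysis set and safety set both require a received treatment, which waiting-list patients do not get during the study, so as written no control patient qualifies for either set

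*Protocol article*

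**What the plan says.** In the Statistical analysis section of the protocol article, two analysis sets depend on exposure. The first: "A full analysis set will include all randomized participants who received at least one treatment and one follow-up". The second: "The safety set will include all randomized participants who received at least one treatment". Neither rule makes an exception for any arm.

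The same section states "The number of end point evaluations in each group will be kept the same as the number of participants in each group", counted at the start of the trial, and plans a repeated-measures ANOVA across all three groups. On how the sets are used, it says: "The statistical analysis of the primary outcome will be analyzed with a full analysis set and per-protocol set separately". The per-protocol set has three conditions. The first is meeting the protocol's criteria; the others are given as "2) participants with measurable primary outcomes, and (3) participants without major violation of the protocol".

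On exposure, the Interventions section says the two acupuncture groups "will receive acupuncture treatments three times per week for a total of 20 treatments". The WL group section says "Patients in the WL group will not receive any acupuncture treatment during the study" and, as an ethical provision, that "20 free acupuncture treatments will be offered after the study is completed".

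**The concern.** The membership rules fit a trial in which every arm is given something. Here one of the three arms is deliberately given nothing before the outcome is measured, so a rule that requires exposure cannot be met by anyone in it.

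The full analysis set is one of only two sets named for the primary outcome. The first aim in the Background, the effectiveness of warm acupuncture, has a randomised comparison only against the waiting list, and that comparison cannot be made in a set without waiting-list patients. The safety set would likewise have no untreated group against which to read lymphedema exacerbation, infection or the week-8 laboratory and ECG results, all of which can change without acupuncture.

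In practice someone will have to set the rule aside for the control arm. The document does not say how, so the population for the primary analysis would be settled informally, after allocation.

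**Working it through.** **Step 1: group sizes.** From Sample size calculation: 30 per group, 20% added for dropout. 30 × 1.20 = 36 per group, and 3 × 36 = 108, as the protocol states. Only the 36 and the 108 are used below; how the 30 was obtained does not bear on this point.

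**Step 2: apply the stated rules.** The table gives the largest number each arm could contribute if every patient were followed up and complied.

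| Arm | Randomised | Sessions during study | Full analysis set | Safety set | Per-protocol set |
|---|---|---|---|---|---|
| LA | 36 | 20 | 36 | 36 | 36 |
| LDA | 36 | 20 | 36 | 36 | 36 |
| WL | 36 | 0 | 0 | 0 | 36 |
| Total | 108 | | 72 | 72 | 108 |

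Excluded from each of the first two sets: 36/108 = 33.3% of those randomised, all from one arm. Retained: at most 72/108 = 66.7%.

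The sessions offered to the waiting list do not alter this. They come after the study is completed, too late to count for a set that analyses change to week 8.

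**Step 3: compare with the rest of the plan.**

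- The repeated-measures ANOVA is specified for three groups. The full analysis set as defined contains two.
- End-point numbers are to equal starting numbers in each group. For the waiting list the rule gives 0 against 36.
- The sample size formula uses K = 3 and includes a waiting-list mean of 3.74 cm. The set as defined supports K = 2.
- The per-protocol conditions contain no explicit requirement of a received treatment. A waiting-list patient who follows the protocol and has a measurable outcome meets them.

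**Step 4: suppose the condition is waived for the waiting list only.** Take follow-up to mean any assessment after baseline (an assumption; the rule does not define it).

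| Patient | Acupuncture arms | Waiting list |
|---|---|---|
| No session, no follow-up | dropped | dropped |
| No session, has follow-up | dropped | kept |
| At least one session, has follow-up | kept | not applicable |

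The arms differ only in the second row. The number of acupuncture patients in that row is not given. The 20% dropout allowance does not supply it, because it is not split by arm or by timing, and it concerns patients who leave, not patients who are assessed without being treated.

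**The case against.** The best reply is that this is a slip of drafting and that nobody would carry it out. The section that defines the set also compares three groups and preserves each group's number, and the trial is allocated 1:1:1 and sized on three arms. An analyst could not drop the waiting list and still run the specified comparison. This stands as a statement of intent. It does not make the rule correct, since the document offers no alternative rule to follow.

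Four stronger readings are tempting, and the document does not support them.

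- A reader might infer that the trial is left with no control arm at all. The per-protocol set is also used for the primary outcome and can keep the waiting list.
- A reader might infer that these patients never receive acupuncture. They are offered it after completion; the accurate statement is that they receive none during the study.
- A reader might infer that, once the rule is waived, waiting-list patients who lose interest stay in while acupuncture patients who leave are dropped. The follow-up condition applies to every arm, so anyone who leaves before any follow-up is dropped whatever the allocation.
- A reader might infer that no safety data exist for the controls. The Safety assessment section calls for all adverse events and schedules week-8 tests without limiting either to treated arms. The arm-level schedule in Table 1 is not shown. What is affected is the set in which these data would be tabulated.

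It is also true that conditioning a safety set on exposure is a common convention. Here it leaves the untreated arm with no defined place in the safety analysis.

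**Conclusion.** The point holds in this form: as written, the full analysis set and the safety set each admit 0 of 36 waiting-list patients and at most 72 of 108 overall, in contradiction to the three-group analysis, the equal-numbers statement and the three-group sample size. The per-protocol set is unaffected.

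This rests on reading treatment as an acupuncture session, which is how the Interventions and WL group sections use the word, and on the article's 36 per arm. Complete loss of the control arm is the literal result, not the likely practice. The realistic problem is that the rule must be overridden and the document does not say how. An override for the waiting list alone leaves the narrower asymmetry of Step 4, which is selection on an event after randomisation that only two arms can experience. Its size is unknown and may be small.

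**What to change.** - **Full analysis set:** delete the condition of a received treatment. Apply one rule to all three arms: randomised participants, analysed in the arm to which they were allocated. Either keep the existing follow-up condition and apply it equally to every arm, or remove it so that the set agrees with the statement that end-point numbers equal starting numbers. State which.
- **Safety set:** define it as all randomised participants, grouped by the treatment actually received, with the waiting list as the untreated group.

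The per-protocol definition need not change for this purpose. The missing-data method is a separate matter and can stay as stated. If the follow-up condition is removed while last observation carried forward is kept, patients with no follow-up would enter with their baseline value and so with zero change, and that choice should be made knowingly.

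The cost is two sentences of wording, with no new data and no change to the design. It should be settled and dated before unblinding, because it decides who is in the primary analysis.

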### Outcomes

#### Primary outcome measures

Various assessment methods are available, but circumference measurement is simple, convenient, low cost, and reliable [12]. Therefore, the primary outcome measures will be the mean change in inter-limb circumference difference from baseline to the end of the 8-week intervention. The circumference will be measured using a measurement tape (Hoechstmass Balzer Gmbh, Sulzbach,Germany) at the wrist crease, 10 cm above the wrist crease, elbow crease, 10 cm above the elbow crease, where the lymphedema is most severe, and at its corresponding location on the unaffected limb. The circumference difference will be assessed at baseline and before intervention at weeks 1–8.

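### Missing week-8 circumference values are to be filled by LOCF, although weekly data and a mixed model that needs no filling are already planned; the primary test should also be labelled.

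*Protocol article*

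**What the plan says.** All places are in the protocol article.

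- **Outcome and schedule** (Primary outcome measures): "the primary outcome measures will be the mean change in inter-limb circumference difference from baseline to the end of the 8-week intervention". On timing: "The circumference difference will be assessed at baseline and before intervention at weeks 1–8". That is one baseline value and up to eight later values per participant.
- **Missing data** (Statistical analysis, in the paragraph on the full analysis set): "The principle of the last observation carried forward will be used in the case of missing data". The sentence after it ties the endpoint count to the starting count: "The number of end point evaluations in each group will be kept the same as the number of participants in each group at the beginning".
- **First method that covers the outcome** (Statistical analysis): "For outcome measures, the mean differences from baseline values to the end of treatment will be compared using ANCOVA".
- **Second method** (same section), which is also applied to volume and skin hardness: "Repeated measures analysis of variance (R-ANOVA) will be used to assess the inter-limb circumference difference".
- **Third method** (same section), which is aimed at circumference difference and the SF-36: "Linear mixed models (for continuous outcome variables) and generalized estimating equations (for categorical outcome variables) will be used to examine the change of intensity".
- **Decision rule** (Statistical analysis): P below 0.05 throughout. The primary outcome is analysed in the full analysis set and in the per-protocol set. No method and no set is labelled primary.
- **Expected loss** (Sample size calculation): 20% dropout, 36 participants per arm.

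**The concern.** The outcome is the change at the end of an 8-week course of 20 sessions. A participant last seen at week 3 has had only part of that course, but LOCF enters the week-3 value as the week-8 result and the analysis treats it as measured. If the response builds up over the course, the filled value understates what week 8 would have shown. The understatement is larger in an arm with a larger effect, earlier dropout or more dropout. The comparison of LDA with LA, a stated aim, can therefore shift for reasons unrelated to the acupoints. Filled values also make the data look more complete than they are.

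This is a stated rule, not a detail left to an unseen analysis plan. It also sits beside a better tool in the same section: a linear mixed model can use every observed week under a missing-at-random assumption with nothing filled in.

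The secondary concern is that three methods address the same outcome at the same threshold, and the text does not say which one carries the conclusion.

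**Working it through.** **Inputs from the protocol article (Sample size calculation).** Pilot values after 20 treatments are LDA 2.34, LA 3.32 and WL 3.74 cm. Expected dropout is 20%, with 36 per arm. The plan's own inflation reproduces as 30 × 1.20 = 36. Twenty percent of 36 is 7.2, or about 7 participants per arm. The plan gives no figure for the effect of LOCF.

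**Effects implied by the pilot, assuming equal baselines and an unchanged waiting list.** LDA: 3.74 − 2.34 = 1.40 cm. LA: 3.74 − 3.32 = 0.42 cm. LDA-LA: 1.40 − 0.42 = 0.98 cm.

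**Assumptions (not in the documents).** Dropout is random, and the last observed week is uniform over weeks 1-7. Two response shapes are tried:

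- linear, t/8, with mean over weeks 1-7 of 4/8 = 0.50;
- early, (1 − exp(−t/2)) / (1 − exp(−4)), with mean over weeks 1-7 of 0.80.

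**Formula.** With dropout d and mean retained fraction m, the share of the true change that survives LOCF is f(d) = (1 − d) + d × m.

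**Equal dropout, 20%.**

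- Linear: f = 0.80 + 0.20 × 0.50 = 0.90. LDA-LA: 0.98 × 0.90 = 0.88 cm. LDA-WL: 1.40 × 0.90 = 1.26 cm. Dilution is 10%.
- Early: f = 0.80 + 0.20 × 0.80 = 0.96. LDA-LA: 0.98 × 0.96 = 0.94 cm. LDA-WL: 1.40 × 0.96 = 1.34 cm. Dilution is 4%.

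A simulation of the linear case (3,000 trials, 36 per arm) gave a mean LDA-LA difference of 0.880 with LOCF and 0.978 using observed data only.

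**Unequal dropout, both arms truly 1.40 cm, 10% versus 30%.**

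- Linear: 1.40 × (0.95 − 0.85) = 0.14 cm, where the truth is zero.
- Early: 1.40 × (0.98 − 0.94) = 0.06 cm.

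**Unequal dropout, LDA 1.40 and LA 0.42 (true difference 0.98), linear.**

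| Dropout LDA / LA | Calculation | LOCF estimate |
|---|---|---|
| 20% / 20% | 1.40 × 0.90 − 0.42 × 0.90 | 0.88 cm |
| 10% / 30% | 1.40 × 0.95 − 0.42 × 0.85 | 0.97 cm |
| 30% / 10% | 1.40 × 0.85 − 0.42 × 0.95 | 0.79 cm |

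In the second row two distortions nearly cancel; in the third they add.

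**Secondary point: chance that at least one of three tests is positive when all arms are equal.** If the tests were independent, it would be 1 − 0.95³ = 0.143. They are correlated, so it was simulated with three arms, nine weekly values and several assumed correlation patterns. Each test alone stays near 5%. The mixed model is represented by a group-by-linear-time test.

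- R-ANOVA read as the between-group effect: about 11% to 13%.
- R-ANOVA read as group-by-time: about 8% to 12%, lowest where neighbouring weeks are most alike.

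Together the range is roughly 8% to 13%.

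**The case against.** Several points on the other side are fair.

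- **Size of the LOCF effect.** No passage says that the response is linear or gradual. With early response the dilution is only 4%. At the plan's single dropout figure, equal in all arms, LOCF shrinks the effect and creates no LDA-LA difference when the two are equally effective. This stands.
- **Unequal dropout.** A reader might infer that LOCF biases the comparison whenever dropout differs by arm. The 10%/30% case above, 0.97 against 0.98 cm, shows that it need not. A reader might also take from simulation that the false-positive rate rises to 7.4% (10% versus 30% dropout) or 11% (5% versus 35%). Those rates need an imbalance between two active arms whose participants do not know which one they receive, and the documents suggest no such imbalance.
- **A partial check exists.** The per-protocol set requires a measurable primary outcome, so it may contain no carried-forward endpoints. The text also does not say that the mixed model would be fitted to filled data. Both points soften the concern, but the stated rule for the full analysis set remains LOCF.
- **Which test is primary.** A reader might infer that the plan has no identifiable primary test. Only the ANCOVA sentence ("the mean differences from baseline values to the end of treatment will be compared using ANCOVA") matches the outcome definition; R-ANOVA and the mixed model can be read as supportive. That is a reasonable reading, though the text does not state it. The 8-13% rate applies only if a positive result on any one test would be claimed as success, and the plan does not say that.

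The choice of LOCF itself is not answered by any of this. It is written as the rule, no alternative for missing data is offered, and the data for a better analysis will be collected anyway.

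**Conclusion.** The concern about LOCF holds. With weekly measurements, expected dropout of 20% and a mixed model already named, LOCF is an inferior rule for a week-8 outcome. Under random dropout spread over weeks 1-7, at 20% in the treated arms, it costs about 4% to 10% of the effect. With equally effective arms and 10% versus 30% dropout it would create a false difference of about 0.06 cm (early response) to 0.14 cm (linear response). Size and direction depend jointly on the effects, the timing and the dropout in each arm. The documents give none of these as trajectories or by-arm rates, so no single bias figure can be assigned to this trial.

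The lack of a labelled primary test is a lesser matter of wording. ANCOVA is the natural inference, and the false-positive rate of roughly 8-13% is what the ambiguity would permit, not what the plan commits to.

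The advantage of analysing observed data was shown under random dropout. It does not extend to dropout that depends on unobserved outcomes.

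**What to change.** 1. Name one primary analysis: a linear mixed model in the full analysis set, using all observed post-baseline weeks without imputation. Include the baseline inter-limb difference as a covariate, arm, week as a categorical factor and arm-by-week, and take the arm contrasts at week 8.
2. Remove LOCF as the main rule, together with the sentence that holds endpoint counts at the starting numbers. LOCF may stay as a sensitivity analysis.
3. Label the week-8 ANCOVA, R-ANOVA and the per-protocol analysis as supportive. R-ANOVA need not be dropped.

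Baseline-adjusted ANCOVA with multiple imputation would be a defensible alternative primary analysis, because it matches the outcome wording directly. The mixed model is preferred here because it is already in the plan and uses the weekly data as collected.

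The cost is a few sentences and one model specification, including the covariance structure. No extra visits, measurements or participants are needed. The downside is reliance on missing-at-random, which should be stated. The change should be fixed before unblinding.
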